### Sample size {14}

This study aims to enrol 120 patients across both sites, with 60 assigned to the sirolimus intervention group and 60 assigned to control. This will provide 80% statistical power (alpha 0.05) to detect an absolute difference of 25% in the proportion of patients who achieve the serological neutralisation titre threshold necessary to provide clinical protection from COVID-19 disease, allowing for a 10% drop-out rate.

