## Assignment of interventions: allocation

### Sequence generation {16a}

Participants will be randomised 1:1 to either sirolimus (intervention) or mycophenolate (control). Randomisation will occur via computer-generated stratified block randomisation with randomly permuted block sizes of 2, 4, and 6. Stratification will occur by site and the response to a two dose COVID-19 vaccine schedule (low responder anti-RBD IgG 0.4 - 99 U/mL; or non-responder, anti-RBD IgG < 0.4 U/mL).

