### Plans for collection, laboratory evaluation, and storage of biological specimens for genetic or molecular analysis in this trial/future use {33}

Blood samples will be taken from participants for immunological assessment at randomisation and at 4–6 weeks following vaccination. Blood will be drawn from participants by clinical research staff and collected in 7 × 9mL lithium heparin and 1 × 8mL CAT serum separator vacutainer tubes. Peripheral blood mononuclear cells (PBMCs) will be isolated from whole blood by density gradient centrifugation in Ficoll-Paque and aliquoted and cryopreserved in liquid nitrogen for batch testing. Sera will be aliquoted and stored at -80°C. Phenotypic and functional assessments of vaccine specific T and B-cell responses will be determined using a variety of laboratory techniques including but not limited to cytometric analysis with intracellular cytokine staining and activation-induced marker (AIM) assays and IFNγ enzyme-linked immunosorbent spot (ELISpot) assays. Using participant serum, the titres of SARS-CoV-2 spike-protein-specific IgG and the capacity of participant serum to neutralise SARS-CoV-2 viral entry into ACE2^+^ cells will be assessed. The capacity of pre- and post-immunisation serum to induce spike-protein-specific antibody-dependent innate immune responses will be measured.

Stool samples will be self-collected by participants using an at home collection kit (OMNIgene GUT OM-200, DNA Genotek, Canada) at baseline and at time of 3^rd^ vaccine dose. Stool samples will be aliquoted and stored at −80°C until batch testing. Analysis of the faecal metagenome will be performed by comparative sequencing of the 16S-rRNA amplicons (V3-V4 region) to identify changes in community structure, relative abundance, and functional characteristics of the gut microbiome.

All biological specimens will be deidentified and labelled with the participants unique study identifier. Stool and blood samples will be stored and maintained in access-restricted laboratory freezers at their corresponding trial site (Adelaide Health and Medical Sciences building, Adelaide, or the Transplant Institute, RPA, Sydney).

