## Statistical methods

### Statistical methods for primary and secondary outcomes {20a}

The primary analysis will be by intention-to-treat, with participants assessed according to their treatment allocation. Participants who develop a positive SARS-CoV-2 PCR result during the study will be excluded from the primary analysis to avoid confounding. A per-protocol analysis will also be reported, with participants who failed to adhere or tolerate sirolimus, and participants who withdrew or were lost to follow-up excluded from the analysis. A sensitivity analyses adjusting for potential confounding may be performed should significant imbalances in baseline characteristics between the treatment groups occur.

The primary endpoint is the proportion of patients who achieved a post-intervention serological neutralisation of live SARS-CoV-2 virus (20.2% of the mean neutralisation level of a standardised cohort of COVID-19 convalescent individuals) in both groups using the chi-square test. An unadjusted and adjusted relative risk (RR) will be calculated. For the adjusted RR estimate, the primary outcome of a threshold SARS-CoV-2 serological neutralisation titre will be analysed using a log-binomial regression model. The initial immune response to a two-dose vaccine schedule (anti-RBD IgG titre; low responder: 0.4–99 U/mL; or non-responder: <0.4 U/mL) will be included in the model as a fixed effect, with study site as a random effect.

Secondary outcomes will be analysed using univariate and multivariate methods dependant on the outcome type. Baseline characteristics and demographic data will be reported as mean ± SD for normally distributed data and median ± IQR for non-normally distributed data, with categorical variables reported as frequencies. All statistical analyses will be described in detail with arising publications. A two-sided significance level of 5% will be used for all analyses.

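### The primary chi-square test ignores the two factors used to stratify randomisation; if response stratum is prognostic it is conservative and loses some power in a trial that closed short of target.

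*Protocol article*

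**What the plan says.** Under Sequence generation {16a}, allocation is 1:1 by "computer-generated stratified block randomisation with randomly permuted block sizes of 2, 4, and 6". The same section adds: "Stratification will occur by site and the response to a two dose COVID-19 vaccine schedule". The response factor separates non-responders (anti-RBD IgG below 0.4 U/mL) from low responders (0.4–99 U/mL). With two sites this makes four strata.

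Statistical methods {20a} compares the primary endpoint "in both groups using the chi-square test. An unadjusted and adjusted relative risk (RR) will be calculated". The adjusted relative risk comes from a log-binomial model with response stratum as a fixed effect and site as a random effect. The article does not make that model the primary test. A further sensitivity analysis may be done "should significant imbalances in baseline characteristics between the treatment groups occur".

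Sample size {14} states: "This will provide 80% statistical power (alpha 0.05) to detect an absolute difference of 25" percent, with 60 per arm and 10% drop-out. Trial status reports that recruitment closed before 120 were enrolled. The number achieved is not given.

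**The concern.** Blocked randomisation within strata forces the arms to be nearly balanced on those strata. Differences between strata then contribute almost nothing to the sampling variation of the treatment difference. The pooled chi-square variance still counts them. If the strata are prognostic, the standard error is too large, the true type I error falls below 5%, and power is lost.

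Response stratum is a plausible prognostic factor. It is antibody level after two doses, and the endpoint is neutralisation above a threshold after a third. The protocol treats it as prognostic: it stratifies on it, puts it in the adjusted model and plans an interaction test with treatment.

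What is at stake is efficiency. The trial cannot recover power by recruiting, so the choice of analysis is one of the few levers left.

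**Working it through.** **1. Reproduce the stated sample size.** Inputs from Sample size {14} and Statistical methods {20a}: two-sided alpha 0.05, 80% power, difference 0.25, 10% drop-out. The control rate is not stated. At 20% vs 45% the pooled rate is 0.325, and

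n = [1.96·√(2·0.325·0.675) + 0.8416·√(0.20·0.80 + 0.45·0.55)]² / 0.25² = (1.298 + 0.537)² / 0.0625 ≈ 54 per arm.

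Then 54/0.9 = 60, as stated. A control rate of 55% (55% vs 80%) gives the same result. At other control rates power with 54 per arm can fall to 74.5%. For 20% vs 45%, chi-square power is 72.4% at 45 per arm, 67.1% at 40 and 54.4% at 30.

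**2. Why the chi-square is conservative.** Take equal strata balanced between arms, with rates p₁ and p₂ under the null and mean p̄. The ratio of the true variance of the difference to the variance the chi-square uses is

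R = [p₁(1−p₁) + p₂(1−p₂)]/2 ÷ [p̄(1−p̄)], and the actual size is about 2·{1 − Φ(1.96/√R)}.

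- No gap: R = 1, size 5%.
- 10%/30%: R = 0.15/0.16 = 0.9375; 1.96/0.968 = 2.02; size 4.3%.
- 20%/60%: R = 0.20/0.24 = 0.833; 1.96/0.913 = 2.15; size 3.2%.
- 15%/65%: R = 0.1775/0.24 = 0.740; 1.96/0.860 = 2.28; size 2.3%.

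**3. Power by simulation.** Uncorrected chi-square against CMH, 54 evaluable per arm (or 120 randomised with 10% random drop-out), equal strata, +25 points in each stratum in the power runs. The stratum rates and shares are assumptions.

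| Control rates (non-/low responders) | Type I error, chi-square vs CMH | Power, chi-square vs CMH |
|---|---|---|
| 20%/20% (not prognostic) | 4.7% vs 4.7% | 80.8% vs 80.5% |
| 10%/30% | 4.4% vs 4.8% | 81.5% vs 82.8% |
| 45%/65% | 4.6% vs 5.0% | 80.8% vs 81.9% |
| 40%/70% | not tabulated | 82.6% vs 85.4% |
| 20%/60% | 3.2% vs 4.8% | 75% vs 82% (about 8 points before rounding) |
| 15%/65% | 2.3% vs 5.1% | 76.0% vs 87.1% |

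The 20%/60% and 15%/65% rows use two response strata with 20,000 to 40,000 trials per setting. The others use permuted blocks of 2, 4 and 6 in four strata, with 8,000 to 10,000 trials.

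At an assumed 30 per arm: not prognostic, 55.5% vs 55.1%; 20%/60%, 50.6% vs 57.4%; 15%/65%, 50.3% vs 62.9%.

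**4. Sensitivity to the assumptions.**
- *Form of the effect.* If the effect is a common odds ratio giving a 25-point marginal difference, the loss at 54 per arm is 84.3 − 82.4 = 1.9 points for 10%/30%, 77.8 − 74.6 = 3.2 for 25%/50% and 89.0 − 83.8 = 5.2 for 5%/35%.
- *Stratum shares.* With 80% non-responders the 15%/65% case narrows to 80% vs 86%.
- *Site.* Adding a site effect (log odds ratio 1.0) to 5%/35% gives 83.6% vs 89.3%, against 83.8% vs 89.0% without it. Site added little there.

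**The case against.** The strongest reply is that an analysis using both factors is already planned without condition, as the adjusted relative risk. The natural reading of {20a} is that the chi-square gives the test and the relative risk gives the estimate. How the two are ranked could be settled in an analysis plan that is not shown. This stands as mitigation and makes the point smaller. It does not remove it, because the article does choose the test, and the test it chooses leaves out factors the authors themselves consider worth adjusting for.

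The size is also open to challenge. The 11-point figure needs a 50-point gap between strata and an overall control rate of 40%. The stated 60 per arm is reproduced at 20% or 55%, and with equal strata an overall rate of 20% cannot hold a gap above 40 points. That objection stands too: small losses are as compatible with the document as large ones.

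Four stronger readings are tempting but unsupported:
- *The p-value is invalid.* The test errs only towards caution.
- *Adjustment for the strata waits on observed imbalance.* That trigger governs only an optional sensitivity analysis.
- *Baseline neutralisation is available as a covariate.* The specimen section {33} says "Blood samples will be taken from participants for immunological assessment at randomisation and at 4–6 weeks following vaccination", but it does not clearly commit to a live-virus neutralisation assay on the baseline serum.
- *The change has no downside.* The last visit was in April 2022 and the trial is open label, so a change of primary test needs a documented decision before results by arm are examined.

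**Conclusion.** The point holds as a matter of efficiency. The named primary test ignores the stratification, and whenever response stratum is prognostic it is conservative and loses power.

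At 54 per arm the loss is 0 points if the stratum is not prognostic, about 1 to 3 points for a 20 to 30 point gap between strata, about 8 for 20%/60% and 11 for 15%/65%. The chi-square type I error runs from 5% down to about 2%. At an assumed 30 per arm the loss is 0 to 13 points. These figures rest on assumed stratum rates, equal strata and +25 points in each stratum; the article gives neither stratum rates, stratum shares nor the number achieved. A reader might infer that a large loss is established. It is not. What is robust is the direction, and that CMH never lost meaningfully: with non-prognostic strata the two tests agreed to within about 0.4 points.

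**What to change.** Before results by arm are examined, do one of the following and record the decision:

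- make the primary test a CMH test stratified by response stratum and site; or
- name the planned adjusted model as decisive, with response stratum and site both as fixed effects, since two sites barely support a random effect.

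Report the crude chi-square as supportive, and say in one sentence which result decides. Log baseline anti-RBD titre, already measured for eligibility, may be added as a prespecified covariate, with a stated rule for titres below 0.4 U/mL. Do not add baseline neutralisation.

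The cost is wording plus a dated justification. The strata are recorded at randomisation, so no new data or assays are needed.

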### Trial design {8}

RIVASTIM-rapamycin is a multicentre, parallel-arm, randomised, controlled, superiority trial, seeking to examine the effect of ceasing mycophenolate and commencing sirolimus in a 3-drug regimen on the immune response to a third dose of mRNA COVID-19 vaccine in kidney transplant recipients who have failed to demonstrate protective immunity following a two-dose vaccine schedule. KTRs on triple therapy who have received 2-doses of a COVID-19 vaccine will be enrolled and their immune response to vaccination assessed by measurement of serological anti-RBD IgG titre. Those with a satisfactory immune response (anti-RBD IgG ≥ 100 U/mL) will exit the study and be advised to receive a third mRNA COVID-19 vaccination as per recommended guidelines. KTRs who fail to demonstrate protective immunity (anti-RBD IgG <100 U/mL) will proceed to randomisation.

Randomisation will occur at a participant level with an allocation ratio of 1:1, stratified by study site and the magnitude of immune response following 2 doses of vaccine (anti-RBD IgG titre; non-responder: < 0.4 U/mL; low responder: 0.4–99 U/mL). An outline of the trial is shown in Fig. 1. Following randomisation patients will either continue their usual immunosuppression regimen of tacrolimus, mycophenolate, and prednisolone (control arm), or have mycophenolate ceased and sirolimus commenced (intervention arm). Sirolimus will be commenced at a standard dose of 2mg daily, with target trough levels of 6 ng/mL and weekly dose titration. Tacrolimus dosage will be adjusted to achieve trough concentration within a range of 3–6 ng/mL. Following a 4-week lead in period, participants will receive a third dose of mRNA COVID-19 vaccine, with the subsequent antibody response measured at 4–6 weeks post vaccination. Participants will continue immunosuppression as per group at least until the time of antibody assessment, and thereafter as determined by their usual nephrologist. The first study participant was enrolled on the 8 November 2021 and recruitment continued through to 15 February 2022, with the final study visit of the last recruited patient in April 2022.

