## Data collection and management

### Plans for assessment and collection of outcomes {18a}

Trial data are collected prospectively by trial staff and entered on to web-based electronic case record forms (eCRF) maintained on a bespoke REDCap database.

Clinical and laboratory data are collected by study staff from the participant’s electronic medical record. Safety laboratory tests (haematology, chemistry, urinalysis) and enrolment criteria (anti-RBD IgG) are performed at the hospital laboratory of each study site. Blood samples for immunological assessment will be collected by clinical research staff and processed in the on-site immunology laboratory at the Royal Adelaide Hospital. Estimation of participants’ habitual diet will be captured using a 4-day food diary, completed at the time stool samples are collected. Validated questionnaires are completed by participants to capture health-related quality of life (EQ-5D) information.

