### Methods for additional analyses (e.g. subgroup analyses) {20b}

Subgroup analyses will be performed to examine for statistical interaction between the treatment arm and (1) initial response to 2-dose vaccine schedule (non-responder or low-responder) and (2) duration between previous vaccine dose (less than, or greater than 6 weeks) and randomisation. Patients who develop primary COVID-19 infection during the study period will have both primary and secondary outcomes analysed as a pre-specified subgroup analysis.

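### The adjusted relative risk uses the baseline antibody titre only as two categories, one of them about 250-fold wide, and so gives up some efficiency; the analysis is valid and the chi-square test is unaffected

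*Protocol article*

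**What the plan says.** Section {20a} of the protocol article plans two things for the primary endpoint. The proportions reaching the neutralisation threshold are compared "in both groups using the chi-square test". An unadjusted and an adjusted relative risk (RR) are also reported, and for the adjusted one the outcome "will be analysed using a log-binomial regression model". Its covariate is the two-dose response in two classes: "anti-RBD IgG titre; low responder: 0.4–99 U/mL; or non-responder: <0.4 U/mL) will be included in the model as a fixed effect". Site enters as a random effect. The two classes are those used to stratify randomisation in sections {8} and {16a}.

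The titre is held as a number. Section {8} says that enrolled recipients have "their immune response to vaccination assessed by measurement of serological anti-RBD IgG titre", and eligibility turns on 100 U/mL. Section {18a} says that "enrolment criteria (anti-RBD IgG) are performed at the hospital laboratory of each study site". Baseline serum exists as well, since section {33} states: "Blood samples will be taken from participants for immunological assessment at randomisation and at 4–6 weeks following vaccination".

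No section enters the titre as a continuous or log-transformed covariate. The only other adjustment in {20a} is an optional sensitivity analysis if baseline imbalance appears.

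**The concern.** By stratifying on the size of the two-dose response, the protocol treats that size as prognostic. The model then keeps only the cut at 0.4 U/mL. A participant at 95 U/mL is just below the level that section {8} calls satisfactory, and one at 0.5 U/mL is 200-fold below it (100/0.5). Both get the same covariate value.

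Stratified randomisation balances the two classes between arms. It does not balance titre within the low-responder class, and the adjusted model cannot correct a chance difference there. What is at stake is precision in the adjusted RR. That matters somewhat more here because the Trial status table says recruitment closed before the target of 120 was reached.

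**Working it through.** **1. Width of the category.** Limits from {20a}: 99/0.4 = 247.5-fold, and log10(247.5) = 2.39. By contrast, 95/0.5 = 190-fold between two participants coded alike.

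**2. The plan's sample size, to anchor the event rates.** Section {14} gives 60 per arm, 80% power, alpha 0.05, a 25-point difference and 10% drop-out. It states no control rate. Try 20% v 45%, with mean 0.325:

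- n = [1.960·√(2·0.325·0.675) + 0.842·√(0.20·0.80 + 0.45·0.55)]² / 0.25²
- = [1.298 + 0.537]² / 0.0625 = 53.9, so 54 per arm
- 54/0.9 = 60 per arm, which matches the plan

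The same formula at 30% v 55% gives 68 per arm after drop-out, and chi-square power of about 0.75 at 54 per arm. So 20% v 45% fits the plan's figure and 30% v 55% does not. Both are assumptions, and results are shown for each.

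**3. Gain from adding log10 titre to the category.** The article gives neither the share of non-responders, nor the titre distribution, nor how strongly titre predicts outcome. All three are assumed and varied.

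| Setting | Assumptions | Category only → plus log10 titre |
|---|---|---|
| 20% v 45%, 54 per arm, standardised RR from a logistic model | 40–80% non-responders; titre uniform on the log scale, 0.4–100 U/mL; no slope within class | power 0.77–0.80 → 0.77–0.79 |
| Same | log-odds slope 0.7 per log10 | 0.79–0.80 → 0.80–0.81 |
| Same | slope 1.5 per log10 | 0.83–0.85 → 0.86–0.88 (gain 2–5 points) |
| 25% v 50%, same method | slope 2.5 per log10 | gain 2.5–9 points, e.g. 0.87 → 0.96 |
| 30% v 55%, 54 per arm, standardised risk difference | 35–50% non-responders; correlation of baseline with post-dose titre 0.4–0.75 | gain 0–5 points; variance lower by 1–13% |
| Same, 40 per arm | same | gain 1–7 points |
| 20% v 45% and 30% v 55%, 40 or 54 per arm, modified Poisson or standardised logistic | 40–60% non-responders; correlation 0.4–0.75 | gain about 0–9 points, no shift in the estimate |

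Monte Carlo error in the first four rows is about 1 point. For the standardised risk difference, simulated type I error was 5.5% with the category and 5.6% with log titre added.

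**4. The same change inside the log-binomial model.** Here the extra covariate causes trouble.

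- Ordinary fits, settings of the last row: successful in 90–100% of trials with the category, and in 2–60% with log titre added.
- Ordinary fits, data generated on the logit scale: failures in 0–5% with the category, and in 5–93% with log titre added.
- Constrained maximum likelihood, 30% v 55%, 250 trials per setting, no site effect: a fitted probability of 1 in 0–2% of trials with the category and in 50–97% with log titre. The true log RR is ln(0.55/0.30) = 0.61. The mean estimate was 0.55–0.62 with the category and 0.48–0.59 with log titre, lower in all 12 settings.

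The gain in step 3 therefore belongs to modified Poisson or logistic standardisation. It cannot be claimed for the log-binomial model as written.

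**The case against.** The strongest reply is that nothing here is an error. Adjusting for the stratification factor as randomised is standard and valid, and the article contradicts itself nowhere on this point. That stands: the matter is efficiency only, and the category should stay in the model.

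The reply goes on that the headline comparison is an unadjusted chi-square test, so no covariate can change it. That stands too. A reader might infer that the power of the primary test suffers, but {20a} does not support this; only the adjusted RR is affected.

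A reader might also infer that adding the titre is free. It is not, in the model the article names: step 4 shows frequent failure and a pull towards the null. The change needs a different estimator.

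It can be added that the benefit may be nil, since the slope within the low-responder class is unknown. That is correct, and it is the lower end of the range. The optional sensitivity analysis for imbalance answers the concern only in part, because it is decided after the data are seen and names no covariates.

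Finally, a reader might extend the criticism to the interaction tests in {20b}, which use the same two response classes and "duration between previous vaccine dose (less than, or greater than 6 weeks) and randomisation". These are supportive analyses with cuts stated in advance. Numeric interaction terms would impose a linear form, and no loss has been shown. That extension is not made here.

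**Conclusion.** The adjusted RR reduces a baseline value known for every participant to two classes, one of them 247.5-fold wide. This is a valid, unbiased analysis that gives up some efficiency. Under the assumed rates, titre distributions and correlations, adding log10 titre raises the power of the adjusted analysis by about 0 to 9 points. At 20% v 45%, the rates that reproduce the plan's 60 per arm, the simulation at 54 per arm gave 0 to about 5 points. There is no gain if titre does not predict outcome within the low-responder class. The figures hold for modified Poisson regression or logistic standardisation.

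A reader might take the width of the category as evidence of a biased or invalid primary analysis. The documents do not support that: allocation is randomised and stratified on these classes, the model adjusts for them, and the chi-square test stands as it is.

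**What to change.** In the model for the adjusted RR in {20a}:

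- keep the two-class response and site;
- add log10 baseline anti-RBD titre, with values below 0.4 U/mL set to one fixed value, so that the class indicator absorbs the floor;
- estimate the adjusted RR by modified Poisson regression with robust standard errors, or by standardisation from a logistic model, in place of the log-binomial fit, and name one of the two in advance.

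The chi-square test, the unadjusted RR and the subgroup section stay as they are. No new data are needed. The cost is one extra degree of freedom and a changed estimation method for the adjusted RR. The choice should be recorded before outcomes are compared by arm.

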## Methods: participants, interventions, and outcomes

### Study setting {9}

The trial will be conducted at the renal transplant units of two tertiary referral hospitals in Australia: (1) The Royal Adelaide, Hospital, Adelaide, South Australia, and (2) The Royal Prince Alfred Hospital, Sydney, New South Wales.

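### The adjusted relative risk is to come from a log-binomial model with a random effect for only two sites; the site variance cannot be reliably estimated and the fit may fail, so the estimate may not be obtainable as written

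*Protocol article*

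**What the plan says.** The section on statistical methods for primary and secondary outcomes {20a} gives three analyses of the primary endpoint. The proportions are compared "in both groups using the chi-square test". Then "An unadjusted and adjusted relative risk (RR) will be calculated". For the adjusted one, the outcome "will be analysed using a log-binomial regression model", and the two-dose response stratum "will be included in the model as a fixed effect, with study site as a random effect".

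The number of sites is explicit. Study setting {9} places the trial at "the renal transplant units of two tertiary referral hospitals in Australia", and Sample size {14} says "This study aims to enrol 120 patients across both sites". Site is also a randomisation factor: "Stratification will occur by site and the response to a two dose COVID-19 vaccine schedule" (Sequence generation {16a}). The Trial status table reports that recruitment closed before 120 patients were enrolled; the number reached is not given.

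**The concern.** The protocol fixes the family, the link and the role of each covariate, so this is a stated choice and not a detail left for later. Two features of it suit the design badly.

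- **Two-level random effect.** A random effect summarises sites by a variance. Two sites give one contrast, and a variance cannot be learned from one contrast with useful precision. Nothing is saved either: a fixed site effect also takes one parameter.
- **Log link.** A log-binomial model does not keep fitted probabilities below 1. Fitting can stop without converging or end on the boundary. A normal site effect on the log scale adds to this, because it has no upper bound.

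At stake is the only primary-outcome estimate specified to use both stratification factors. It may come back with the site term reduced to nothing, or not come back at all.

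**Working it through.** **Inputs from the protocol article:** 2 sites; 120 planned; 10% drop-out, so 120 × (1 − 0.10) = 108 analysed. **Assumed, because the article does not give them:** response rates by arm and stratum, the site SD on the log scale, and N = 60 as an example of a shortfall. The protocol states no figure for this model, so there is none to reproduce.

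**Model as written.** log P(response) = b0 + b1·arm + b2·stratum + u(site), with u ~ N(0, σ²) and two values of u.

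**Step 1: best case for the variance.** Suppose both site effects were known without error. Their sample variance s² has 2 − 1 = 1 degree of freedom, and the 95% limits for σ² are s²/χ²(0.975; 1) and s²/χ²(0.025; 1).

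- Lower: 1/5.02 = 0.20 times s²
- Upper: 1/0.000982 = 1,018 times s²
- For the SD: √0.20 = 0.45 and √1,018 = 31.9 times

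Real data can only do worse, since the site effects must themselves be estimated.

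**Step 2: how often the variance is estimated as zero.** Maximum likelihood with Gauss-Hermite quadrature; 54 patients per site; control rates 20% and 45% and sirolimus rates 35% and 70% in the two strata; 200 trials per setting; zero means an estimated SD below 0.03.

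| True site SD | Estimated as zero |
|---|---|
| 0 | 86% |
| 0.1 | 74% |
| 0.2 | 56% |
| 0.3 | 47% |

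The first two rows matter little, because there is little to adjust for. The last two show the term vanishing about half the time when sites do differ.

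**Step 3: a second simulation with other assumed rates.** 120 runs per setting; stratum relative risk 1.5. The last two columns refit with site as a fixed effect.

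| N | Rates | Site SD | Zero | 95th percentile of SD | Log-binomial, site fixed: failed | Modified Poisson, site fixed: failed |
|---|---|---|---|---|---|---|
| 108 | 25% v 50% | 0.3 | 45% | 0.92 | 9% | 0% |
| 108 | 35% v 60% | 0.15 | 56% | 0.39 | 9% | 0% |
| 60 | 25% v 50% | 0.3 | 62% | 1.21 | 15% | 0% |
| 60 | 35% v 60% | 0.15 | 76% | 0.31 | 14% | 0% |

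At a true SD of 0.3, the 95th percentile is 0.92/0.3 = 3.1 to 1.21/0.3 = 4.0 times the truth. In 14% to 28% of runs in these rows, the fitted mixed model implied a probability above 1 within two SDs of the site effect. Monte Carlo error is up to √(0.25/120) = 4.6 points.

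**Step 4: range of the fit problem.** Further runs with site fixed and other assumed rates gave log-binomial failure or a boundary solution in about 0.5% to 6% (N = 108, no site effect), 16% to 42% (N = 108, site SD 0.3) and 6% to 50% (N = 60). Modified Poisson with fixed site returned an estimate every time. In the Step 3 simulation, its 95% interval for the relative risk covered the truth in 90% to 98% of runs over all settings tried, including a high-response setting not tabulated.

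**Step 5: what losing the site term does to the relative risk.** N = 108, arms balanced within site-by-stratum cells, control rates 20% and 45%, relative risk 1.6, modified Poisson, 600 runs per setting, site SD 0 to 0.3. The log relative risk with and without site differed by a median of at most 0.0011 and a 95th percentile of at most 0.013, that is exp(0.013) = 1.013, or 1.3%. At SD 0.3 the mean standard error was 0.224 without site and 0.218 with it, a ratio of 1.03; coverage was 93% to 96% without and 93% to 95% with.

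**The case against.** The strongest reply is that the site variance is a nuisance quantity and nothing important hangs on it. Most of that stands. The primary test is an unadjusted chi-square test and the unadjusted relative risk needs no model. Randomisation is 1:1 and stratified by site, and Step 5 shows that dropping site changes the relative risk and its standard error very little. A reader might infer that a collapsed site term biases the treatment effect or undermines the primary result; the documents and the check do not support that.

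A second reply is that the log-link problem depends on response rates that the plan does not state. That also stands. A reader might take the 60% in the Background as the design control rate and conclude that failure is likely. That figure is a third-dose result from another trial, this trial randomises only patients below 100 U/mL after two doses, and Sample size {14} names no control rate. With low rates and no site effect, failure is rare. Part of the failure count also reflects the ordinary fitting algorithm and its starting values; it does not prove that no maximum likelihood estimate exists.

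A third reply is that a fallback for non-convergence belongs in the analysis plan, which is not shown. So it cannot be said that the estimator would be chosen after seeing the data. What remains is the main model, which the protocol does fix.

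**Conclusion.** The point holds in limited form. With two sites, the random-effect variance cannot be reliably estimated: it is often zero and otherwise very imprecise. To call it not estimable would go too far, since software may return a number. This part rests only on the count of sites. The second part, that the log-binomial fit may fail or reach the boundary, is conditional: from under 1% to 50% of runs, according to assumed response rates, site differences and sample size. Closing recruitment below 120 makes the fit more fragile.

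The consequence is confined to the adjusted relative risk, which may not be obtainable as specified. The chi-square test and the unadjusted relative risk are unaffected. It should be fixed, but it is not a condition for a valid primary test.

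**What to change.** Replace the mixed log-binomial specification with one sentence in the analysis plan, to this effect: the adjusted relative risk will be estimated by modified Poisson regression with robust standard errors, with treatment arm, two-dose responder stratum and site (one parameter) as fixed effects. Logistic regression with the same terms and marginal standardisation to the relative risk is an equally good choice; name one of them as the main estimator.

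Both changes are needed. Making site fixed removes the variance problem but leaves the log-link failures in Steps 3 and 4. The cost is one sentence and a slight loss of efficiency against a log-binomial model that happens to converge. The chi-square test, the sample size and the data collected do not change.
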